## Abstract

**Background:**

Experimental studies suggest that angiotensin II plays a central role in the pathogenesis of abdominal aortic aneurysm. This trial aims to evaluate the efficacy of the angiotensin receptor blocker telmisartan in limiting the progression of abdominal aortic aneurysm.

**Methods/Design:**

Telmisartan in the management of abdominal aortic aneurysm (TEDY) is a multicentre, parallel-design, randomised, double-blind, placebo-controlled trial with an intention-to-treat analysis. We aim to randomly assign 300 participants with small abdominal aortic aneurysm to either 40 mg of telmisartan or identical placebo and follow patients over 2 years. The primary endpoint will be abdominal aortic aneurysm growth as measured by 1) maximum infra-renal aortic volume on computed tomographic angiography, 2) maximum orthogonal diameter on computed tomographic angiography, and 3) maximum diameter on ultrasound. Secondary endpoints include change in resting brachial blood pressure, abdominal aortic aneurysm biomarker profile and health-related quality of life. TEDY is an international collaboration conducted from major vascular centres in Australia, the United States and the Netherlands.

**Discussion:**

Currently, no medication has been convincingly demonstrated to limit abdominal aortic aneurysm progression. TEDY will examine the potential of a promising treatment strategy for patients with small abdominal aortic aneurysms.

**Trial registration:**

Australian and Leiden study centres: Australian New Zealand Clinical Trials Registry ACTRN12611000931976, registered on 30 August 2011; Stanford study centre: clinicaltrials.gov NCT01683084, registered on 5 September 2012.

## Background

Abdominal aortic aneurysm (AAA) is a major contributor to mortality in western countries, responsible for over 10,000 annual deaths in the USA and costing the healthcare system more than $3 billion per annum [1, 2]. Over the last decade a number of advances have been made to the management of AAA including the introduction of screening programs designed to identify AAAs before they rupture and the development of sophisticated minimally invasive techniques to repair large AAAs [3, 4]. The introduction of targeted AAA ultrasound screening programs in a number of countries, such as the United States, the United Kingdom and Sweden, is expected to reduce AAA-related mortality. Individuals found to have large AAAs (infra-renal aortic diameter >55 mm) are usually considered for elective surgical repair to prevent potentially fatal AAA rupture. However 90 % of AAAs detected through screening are <55 mm in diameter (small AAAs), and these carry a low risk of rupture [5, 6]. Four trials have suggested that early elective open or endovascular repair does not reduce mortality for patients with AAAs measuring 40 to 55 mm in diameter [7]. Current guidelines therefore advocate that patients with small AAAs be managed conservatively with surveillance comprising repeated imaging and consultations [8]. On average, small AAAs expand 1 to 3 mm per year and up to 70 % of patients will eventually require surgery [9–11]. This current practice of simply monitoring small AAAs is associated with reduced health-related quality of life, possibly due to patients’ concerns that no active treatment is being undertaken [12].

Effective drug therapies that prevent or limit AAA growth may improve health-related quality of life, reduce the need for surgery and prevent mortality in patients unsuitable for AAA repair. There is limited evidence suggesting that the control of atherogenic risk factors alone slows AAA progression [13]. However such treatment is still advised as these individuals are at high risk of acute cardiovascular events [14]. A number of small randomised controlled trials have been conducted in humans in an attempt to discover a drug that limits AAA growth [15, 16]. Only two published studies, using the β-blocker propranolol and the antibiotic doxycycline, included more than 200 patients, and neither study reported a benefit of the medication tested [17, 18]. Drugs shown to slow AAA progression in animal models and observational human studies include statins, macrolides, cyclooxygenase inhibitors and developmental agents such as c-Jun N-terminal kinase inhibitors [19–23]. While statins are well tolerated, they are already indicated and prescribed in most patients with AAAs and therefore difficult to assess for their efficacy in limiting AAA progression [24, 25]. A potential drug to be trialled for AAA ideally requires a number of important characteristics including evidence to support its benefit, a good safety profile from phase II studies or use of the medication in related conditions, and likelihood of good compliance.

There is a large body of evidence suggesting that angiotensin II plays a critical role in AAA formation, progression and rupture [26]. Infusion of angiotensin II via a subcutaneous osmotic pump constitutes a commonly applied mouse model of aortic aneurysm, utilized in hundreds of studies to date [27]. Such angiotensin II-induced AAAs have some features comparable to human AAA, including a similar gene expression profile on microarray analysis; marked inflammatory focus; associated thrombus; and predilection for males and sites of atherosclerosis [28]. Angiotensin II activates the angiotensin II receptor type 1 (AT1) to promote a series of molecular changes implicated in AAA formation including up-regulation of pro-inflammatory cytokines and proteins, such as osteopontin (OPN), osteoprotegerin (OPG), transforming growth factor-beta1 (TGF-β1), and matrix metalloproteinase-9 (MMP-9) [29–31]. The reduction in ascending aortic diameter in patients with Marfan syndrome after 6 months therapy with the angiotensin converting enzyme inhibitor, perindopril, supports a clinical rationale for renin angiotensin system inhibition in humans [32]. The 3 to 7 mm reduction in aortic diameter in this trial was also associated with reduction in circulating TGF-β and MMP levels [33].

Given the current evidence suggesting a central role of angiotensin II in the pathogenesis of AAA, the use of AT1 blockers to potentially slow AAA progression has generated considerable interest. Telmisartan is a potent, long-acting AT1 blocker classically indicated for essential hypertension, heart failure and renal failure. We hypothesise that telmisartan will reduce AAA growth by down-regulation of the AT1 pathway. Telmisartan also has PPARγ agonist activity that is greater than other AT1 blockers [34, 35]. Evidence has accumulated showing PPARγ ligation to inhibit angiotensin II-mediated up-regulation of OPN, OPG, MMP-9 and TGF-β1, which are implicated in AAA [36–39]. In animal models PPARγ agonists limit AAA development, progression and rupture [36, 38, 40]. The combination of AT1 blockade and PPARγ ligation could be very effective in limiting AAA expansion in humans.

Inhibition of AT1 could have benefit over angiotensin-converting enzyme (ACE) inhibition for several reasons: (i) ACE inhibition, unlike AT1 blockade, only indirectly inhibits the angiotensin pathway; (ii) a number of non-ACE angiotensin II producing enzymes have been identified in AAA biopsies, suggesting that ACE inhibition may only partially inhibit the effects of angiotensin II [41, 42]; (iii) part of the blood pressure-lowering effect of ACE inhibitors is attributable to an increase in circulating kinins, which have unknown effects on AAA [43]; and (iv) AT1 blockers demonstrate fewer and less severe side effects compared to ACE inhibitors in some studies [44].

Telmisartan has been shown to inhibit AAA in three different animal model studies [45–47]. AT1 blocker prescription has also been associated with reduced AAA progression in one surveillance study involving 1,269 patients with small AAA [48]. To date, no randomised trials have been conducted to examine the effect of an AT1 inhibitor on AAA progression. This trial seeks to evaluate the efficacy of telmisartan in limiting AAA expansion.

## Methods/Design

### Study design

Telmisartan in the management of abdominal aortic aneurysm (TEDY) is a parallel-design, randomised, double-blind, placebo-controlled trial to assess whether treatment with telmisartan for 2 years will reduce the rate of AAA expansion. The TEDY trial plans to enrol 300 participants with small AAA, defined by a maximum orthogonal infra-renal aortic diameter of ≥35 and ≤49 mm on computed tomographic angiography (CTA) or ultrasound. In order to explicitly assess the impact of AT1 blockade on AAA expansion, TEDY will only include individuals who have no current or planned usage of AT1 blockers or ACE inhibitors. TEDY will not include individuals with an existing indication for AAA repair (according to the treating physician) or expectation that this will be revised within one year. Furthermore, participants will only be included if they have a high likelihood of treatment compliance for 24 months according to their supervising physician. Additional exclusion criteria include contraindications to telmisartan and previous abdominal aortic surgery. A full list of inclusion and exclusion criteria is given in Table 1.

**Table 1 Tab1:** Patient eligibility criteria

**Inclusion criteria**
• Written informed consent
• Infra-renal AAA with maximum orthogonal diameter of ≥35 mm and ≤49 mm on CTA or ultrasound
• No current indication for AAA repair, or expectation that this will be revised in 12 months
• Likely to comply with treatment over 24 months, including seven visits to study centre
**Exclusion criteria**
• Currently taking or likely to start taking an AT1 blocker
• Currently taking or likely to start taking an ACE inhibitor
• Previous abdominal aortic surgery
• Contraindication to telmisartan:
o Renal impairment: creatinine >1.5 x ULN
o Known renal artery stenosis >70 % of one or both renal arteries
o Chronic liver disease (that is, cirrhosis or hepatitis) or abnormal liver function (that is, ALT > 1.5 x ULN)
o Electrolyte imbalance
o Active gout

*AAA,* abdominal aortic aneurysm; ACE, angiotensin converting enzyme; ALT, alanine transaminase; *AT1,* angiotensin II receptor type 1; CTA, computed tomographic angiography; *ULN,* upper limit of normal

### Randomisation and follow-up

The overall design of the TEDY trial is shown in Fig. 1. At the initial visit, individuals will be considered for inclusion in the trial (Table 1) and if eligible, informed consent will be sought. Individuals will undergo a short health survey, clinical examination by a medical officer, resting brachial blood pressure, resting ankle-brachial index, and collection of fasting blood samples for analysis of lipid profile, blood glucose, inflammatory markers, AAA biomarkers, liver function and renal function. An additional blood sample will be stored for future genetic, protein and lipidomic analyses. A baseline CTA and ultrasound will be obtained for detailed measurements of the AAA.

**Fig. 1 Fig1:**
[figure not shown]
Design of the Telmisartan in the management of abdominal aortic aneurysm (TEDY) Trial

Eligible participants who have provided written informed consent will return for a randomisation visit, during which they will be allocated to either telmisartan (40 mg od daily) or matching placebo (once daily) for 24 months. Patients will be randomised by a blinded health professional through the secure trial website, coordinated by an independent trial centre. Treatment allocation will be determined by a computer-generated random number sequence that is stratified by study site and initial aortic diameter (35 to 39 mm, 40 to 44 mm, and 45 to 49 mm). Random number sequences will correspond to serial numbers on concealed study packaging. Only the trial drug centre and the Data and Safety Monitoring Board (DSMB) will know the identity of pre-packaged drugs. The Stanford study centre will utilize an independent randomization procedure implemented locally, whereby ID numbers are randomly allocated to the two study groups using randomization software (www.tufts.edu/~gdallal/randomize.htm). The resultant randomization key will be provided to the on-site pharmacy, which dispenses study medication to participants according to the condition assignment prescribed by the key.

Following randomisation, participants will receive their allocated study medication and subsequent instruction on the dosing regimen. Individuals will be contacted by phone 2 weeks after randomisation and asked about adherence to study treatment and known medication side effects. Phone consultations will be repeated at 9, 15 and 21 months. Follow-up visits will occur at 3, 6, 12, 18 and 24 months, during which the occurrence of trial endpoints and adverse events will be appraised. Participants will receive ongoing health questionnaires, clinical examination, blood tests and imaging according to Table 2. All participants, including those in whom allocated medication is discontinued, will be invited to follow up for the duration of the study in the absence of AAA repair. Final follow-up will occur at 24 months after randomisation, at which point the participant will discontinue the prescribed medication.

**Table 2 Tab2:** Visit schedule

	Study time points (months)										
	0	0	½	3	6	9	12	15	18	21	24
Assessment	Visit 1	Visit 2	Phone Call	Visit 3	Visit 4	Phone Call	Visit 5	Phone Call	Visit 6	Phone Call	Visit 7
Consent	x										
Enrolment/randomisation		x									
CT angiography	x						x^a^				x
Ultrasound	x				x		x		x		x
Blood test (safety)	x			x			x				x
Blood collection (study)	x				x		x		x		x
Resting brachial BP	x			x	x		x		x		x
SF-36 questionnaire	x						x				x
Physical assessments	x^±^			x	x		x		x		x
Medical examination	x			x			x				x
Resting ABI	x						x				x
Collection of study medication		x			x		x		x		
Return of study medication					x		x		x		x
Event outcomes				x	x		x		x		x
AE and compliance check			x	x	x	x	x	x	x	x	x

Physical assessments include: resting BP, resting heart rate, weight, hip and waist measurements, ^±^indicates an additional assessment of height. ABI, ankle brachial-index; AE, adverse effects; BP, blood pressure; CT, computed tomography

^a^The Leiden and Stanford study centres will not perform 12-month CTAs due to local ethics regulations. The Stanford centre will utilize a slightly different study schedule. In place of the 2-week phone call and 3-month visit, participants will attend for a safety visit at 1 month for assessment of adherence to study treatment and medication side effects. Study medications will be prescribed at 3-month intervals with AE and compliance checks at 3, 9, 15 and 21 months

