### Endpoints

The trial primary endpoint will be the difference in AAA growth between the intervention and control groups over 24 months. AAA growth will be assessed by 1) maximum infra-renal aortic volume on CTA, 2) maximum orthogonal diameter on CTA, and 3) maximum diameter on ultrasound. Infra-renal aortic volume can be measured in a reproducible way and changes in it appear to provide a more sensitive means to assess AAA growth [49]. It is expected that a number of participants may not receive a CTA at 24 months due to drop-out, for example due to requirement for AAA surgery. We therefore have also included ultrasound measured AAA growth as a primary endpoint since ultrasound assessments will be performed every 6 months.

CTA will be obtained at entry, 12 and 24 months depending on local ethics guidelines (CTA at entry and 24 months only for Stanford and Leiden study centres). Assessment of infra-renal aortic volume will be performed according to a previously established protocol at the main study centre (mean inter-observer coefficient of variation = 2.7 %) [49]. The total volume of the infra-renal aorta, including the aortic wall and lumen, will be estimated using a semi-automated program that we have previously established to be reproducible [49]. In short, axial regions of interest are drawn around the aorta from the slice inferior to the origin of the lowest renal artery to the slice superior to the bifurcation of the aorta. The areas of these regions of interest are summated using CT analysis software to yield an overall volume. The maximum orthogonal AAA diameter on CTA is a measurement of infra-renal aortic diameter perpendicular to the lumen, devised to avoid over-estimation of tortuous AAAs. We have previously reported a reproducible protocol to measure orthogonal aortic diameter (mean inter-observer coefficient of variation = 3.5 %) [50]. Initially, seeds are placed in the centre of the infra-renal aorta from the renal arteries to the aortic bifurcation. Curved multi-planar reconstruction is then used to reconstruct the aorta perpendicular to its axis. The reconstructed aorta is subsequently scouted to find the region of maximum diameter, taking many measurements. The largest diameter is taken to be the maximum orthogonal diameter.

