Ultrasound measurements will be undertaken at entry, 6, 12, 18 and 24 months. Maximum anteroposterior and transverse infra-renal aortic diameter will be measured by experienced sonographers using a 3.75-MHz transducer and ultrasound machines present in vascular laboratories of each centre. Diameters will be measured in the plane of the aorta with callipers placed on the outer part of the aortic wall. The largest external anterior-posterior and transverse AAA diameters will be recorded. The location at which the maximum diameter is measured will always be within the infra-renal aorta but will be selected based on the maximum diameter not particular location within this artery segment. The intra-observer reproducibility of ultrasound measurements has been assessed at major participating centres and shown to be good (coefficient of repeatability ≤1.6 mm for four reporting centres) [18, 31]. Central analysis of both CTA and ultrasound images will be performed at the study centre.

Secondary endpoints include change in resting brachial blood pressure, AAA biomarker profile, and health-related quality of life. Resting brachial blood pressure will be measured at entry, 3, 6, 12, 18 and 24 months. Three blood pressure measurements will be recorded at 3-minute intervals, with the average blood pressure used as the representative value. Blood will be taken at entry, 6, 12, 18 and 24 months to assess changes in circulating AAA biomarkers. The AAA biomarker panel will include OPN, OPG, D-dimer, TGF-β1 and MMP-9, and will be measured centrally. These circulating proteins have been selected based on extensive evidence suggesting that they have a central role in AAA pathology [39, 51]. Health-related quality of life will be assessed by the Short Form-36 (SF-36) questionnaire collected at entry, 12 and 24 months. The SF-36 has previously been validated for use in elderly patients with vascular disease [52, 53].

Additional outcome data recorded will include requirement for AAA repair surgery as determined by the treating vascular surgeon, AAA rupture, all-cause mortality, acute cardiovascular events, withdrawal from study medication, drug safety and changes in background medication. Medication compliance will be assessed by hand-counting of pills during scheduled visits.

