### Statistical analysis

The principal analysis of primary and secondary endpoints will be based on intention to treat at the time of randomisation. All patients who meet the eligibility criteria, provide written informed consent and are enrolled in the study will be included in the primary analysis, regardless of adherence to treatment medication. The efficiency of randomisation will be assessed by comparing the distribution of recognized determinants of AAA progression and also background medication use prior to the study between the treatment and control groups.

The primary efficacy parameter is the between treatment groups difference in mean growth in AAA over 2 years as estimated by the maximum AAA volume on CTA, maximum orthogonal diameter on CTA, and maximum diameter on ultrasound. If there were to be no drop-outs, the observed mean progression over 2 years would be compared and tested using a two-sample t-test. However, it is expected that a non-negligible proportion of patients will drop out before 2 years due to aneurysm repair. Aneurysm growth will therefore be analysed by a linear mixed model, specifying zero difference between treatment groups at baseline. The model will have up to 11 repeated dependent measurements: three CTA volume measurements, three CTA diameter measurements, and five ultrasound measurements.

The fixed part of the model will contain the following covariates: Time for CTA measurements as a categorical, time for ultrasound measurements as a categorical, treatment, interaction between treatment and CTA time, and interaction between treatment and ultrasound time. The covariance part of the model will constitute a linear covariance matrix containing the following parameters: Variance of CTA measurements, variance of ultrasound measurements and covariance parameters. Without reference to the fixed part of the model, the goodness of fit of the assumed covariance model will be investigated. If necessary, the model will be extended with additional terms. The analysis will be performed using the PROC MIXED procedure on SAS (Cary, North Carolina), which is capable of fitting arbitrary linear covariance matrices. The main null hypothesis that will be tested is based on the treatment effect as estimated by this model at 24 months on CTA and ultrasound measurements.

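### Scheduled follow-up stops at AAA repair, so blood pressure, SF-36, mortality, cardiovascular and safety data may be cut short by an event that treatment could influence

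*Protocol article*

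**What the plan says.** Under Randomisation and follow-up, the protocol article says that all participants, including those no longer taking study drug, "will be invited to follow up for the duration of the study in the absence of AAA repair". The same section sets the planned end: "Final follow-up will occur at 24 months after randomisation".

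Two other places treat repair as loss to follow-up. Endpoints says that some participants "may not receive a CTA at 24 months due to drop-out, for example due to requirement for AAA surgery". Statistical analysis says that "it is expected that a non-negligible proportion of patients will drop out before 2 years due to aneurysm repair", and answers this with a linear mixed model for aneurysm growth.

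The outcomes extend well beyond growth. Endpoints states: "Secondary endpoints include change in resting brachial blood pressure, AAA biomarker profile, and health-related quality of life". Among additional outcomes it lists "AAA rupture, all-cause mortality, acute cardiovascular events, withdrawal from study medication, drug safety". On the analysis set, Statistical analysis states: "The principal analysis of primary and secondary endpoints will be based on intention to treat at the time of randomisation". The Abstract describes a "placebo-controlled trial with an intention-to-treat analysis".

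**The concern.** Ending growth measurement at repair is unavoidable. The follow-up sentence, however, is not limited to imaging. Read as written, it governs the whole Table 2 schedule, including blood pressure, SF-36, event outcomes and adverse-event checks.

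Repair is not a neutral reason for stopping. It follows from growth, and the Background says that a drug limiting growth may reduce the need for surgery. On the trial's own hypothesis, repair would be more frequent on placebo. Follow-up would then stop more often in that arm, just before any operative or post-operative events.

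Three things are at stake:
- a 24-month comparison of blood pressure and SF-36 in everyone randomised;
- a fair count of deaths and cardiovascular events by arm;
- the completeness of the serious-complication data that the monitoring board weighs when it considers stopping (Safety).

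**Working it through.** The point rests mainly on the text. The arithmetic only bounds its size.

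**1. Is this a rule or an omission?** The follow-up sentence separates two groups: those who stop the drug stay in, and those who have repair do not. Endpoints and Statistical analysis both call repair drop-out. No section describes any contact after repair. It is therefore a stated rule, not a detail left out of a condensed article.

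**2. Which outcomes are affected?**

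| Outcome | Status in the article | Measurable after repair? | Remedy stated for repair drop-out |
|---|---|---|---|
| AAA growth | Primary | No | Linear mixed model |
| Blood pressure, SF-36 | Secondary, intention to treat | Yes | None |
| Mortality, cardiovascular events, safety | Additional | Yes | None |

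The biomarker panel is also a secondary endpoint. It is not pressed here because it is tied to the aneurysm itself.

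**3. Upper limit on numbers.** Sample size and power calculations gives about 20 % drop-out at 24 months from all causes: 0.20 × 300 = 60. It gives no reasons and no share due to repair.

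**4. What the plan's growth figures imply.** Inputs: entry diameter at most 49 mm (Table 1); repair usually considered above 55 mm (Background); growth mean 1.20 mm/y, SD 1.16 (Sample size). Assume normal growth at a constant rate over 2 years. The rate needed to pass 55 mm in 24 months is (55 − entry diameter)/2, and z = (rate − 1.20)/1.16.
- Entry 49 mm: rate 3.0, z = 1.80/1.16 = 1.55, probability about 6 %.
- Entry 47 mm: rate 4.0, z = 2.80/1.16 = 2.41, about 0.8 %.
- Entry 45 mm: rate 5.0, z = 3.80/1.16 = 3.28, about 0.05 %.

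Repair for other reasons would raise these figures. So would faster growth, since the Background quotes 1 to 3 mm per year for small aneurysms. Even so, 20 % of all entrants is well above what 1.20 mm/y implies.

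**5. Follow-up lost, for an assumed repair share r of 5 to 20 %.** Planned follow-up is 300 × 2 = 600 person-years. If repair times are uniform over 24 months, each repaired participant loses 1 year on average. The loss is 300 × r × 1 = 15 to 60 person-years, or 2.5 to 10 %. Table 1 excludes people expected to need repair within 12 months. If all repairs fell uniformly in year 2, the average loss would be 0.5 year, giving 7.5 to 30 person-years (1.25 to 5 %).

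**6. Possible effect on a mortality comparison (all rates assumed).** Take 24-month repair risks of 20 % on placebo and 14 % on telmisartan, a death rate h of 3 % per year in both arms, and extra mortality at repair of 0 to 5 %. With repair hazard λ = −ln(1 − r)/2, the risk of a recorded death before repair is h/(h + λ) × [1 − exp(−2(h + λ))].
- Placebo: λ = 0.1116, recorded risk 5.23 %. With full follow-up: 5.82 to 6.77 %.
- Telmisartan: λ = 0.0754, recorded risk 5.41 %. With full follow-up: 5.82 to 6.48 %.
- Telmisartan minus placebo: about +0.2 points recorded, against 0 to −0.3 points with full follow-up.

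For scale, with 150 per arm and a risk of 5.8 %, the standard error of the difference is √(2 × 0.058 × 0.942/150) = 0.027, or 2.7 points. The sign can change, but the shift is small beside sampling error, and the example uses the upper limit for repair on placebo.

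**The case against.** **The rule does not stop event recording.** The sentence says who is invited to follow-up. It does not bar recording later deaths or serious adverse events. Endpoints lists mortality and cardiovascular events without a cut-off at repair. Safety counts in-patient treatment as serious, so an in-patient repair admission would itself be reportable, and the monitoring board reviews all adverse events. This stands in part: a reader might infer that deaths after repair will certainly go uncounted, and the text does not say so. What remains is that sites following the sentence have no scheduled contact at which to learn of such events.

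**Intention to treat is not broken.** A reader might infer that the intention-to-treat claim fails. The documents do not support that. The set is defined as all eligible, consenting, enrolled patients whatever their adherence, and lost follow-up creates missing data without removing anyone from it. Moreover, the endpoint-level sentence covers primary and secondary endpoints only, so mortality, cardiovascular events and safety fall only under the general description in the Abstract.

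**The 20 % is not a repair rate.** A reader might take most of the 60 expected drop-outs to be repairs. The sample-size section gives no reason for the figure, and the growth data point lower. This objection stands.

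**Pre-repair values answer a legitimate question.** Blood pressure and SF-36 after surgery include the effect of the operation. That supports keeping a pre-repair analysis as supportive. It does not support failing to collect the data, because the wider comparison then cannot be made.

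**Conclusion.** The concern holds in a limited form. The protocol article ends scheduled follow-up at an event that treatment may change, for outcomes that remain measurable, and states a remedy for growth alone. The loss may therefore be informative and differ by arm.

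The size cannot be computed because no repair rate is given. Sixty of 300 is a ceiling, and the true number is probably well below it given entry at 49 mm or less and mean growth of 1.20 mm/y. In the assumed example the mortality difference moves by 0.2 to 0.5 percentage points (from between 0 and −0.3 to +0.2), against a standard error of 2.7. The bias is probably modest. The change is still worth making because it is cheap and follow-up not collected may be unrecoverable.

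**What to change.** Amend the sentence in Randomisation and follow-up so that AAA repair ends only the aortic growth measurements. State that vital status, cardiovascular events, serious adverse events, SF-36 and blood pressure are collected to 24 months in all randomised participants, at the visits or calls already in Table 2 (or in the Stanford schedule given in its footnote). Keep an analysis restricted to pre-repair blood pressure and SF-36 as supportive, since later values will include the effect of surgery.

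The cost is a small protocol amendment and some extra contacts with repaired participants. The growth model needs no change.
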